## Abstract

**Background:**

Integrated care, in particular the ‘Blended Collaborative Care (BCC)’ strategy, may have the potential to improve health-related quality of life (HRQoL) in multimorbid patients with heart failure (HF) and psychosocial burden at no or low additional cost. The ESCAPE trial is a randomised controlled trial for the evaluation of a BCC approach in five European countries. For the economic evaluation of alongside this trial, the four main objectives were: (i) to document the costs of delivering the intervention, (ii) to assess the running costs across study sites, (iii) to evaluate short-term cost-effectiveness and cost-utility compared to providers’ usual care, and (iv) to examine the budgetary implications.

**Methods:**

The trial-based economic analyses will include cross-country cost-effectiveness and cost-utility assessments from a payer perspective. The cost-utility analysis will calculate quality-adjusted life years (QALYs) using the EQ-5D-5L and national value sets. Cost-effectiveness will include the cost per hospital admission avoided and the cost per depression-free days (DFD). Resource use will be measured from different sources, including electronic medical health records, standardised questionnaires, patient receipts and a care manager survey. Uncertainty will be addressed using bootstrapping.

**Discussion:**

The various methods and approaches used for data acquisition should provide insights into the potential benefits and cost-effectiveness of a BCC intervention. Providing the economic evaluation of ESCAPE will contribute to a country-based structural and organisational planning of BCC (e.g., the number of patients that may benefit, how many care managers are needed). Improved care is expected to enhance health-related quality of life at little or no extra cost.

**Trial registration:**

The study follows CHEERS2022 and is registered at the German Clinical Trials Register (DRKS00025120).

**Supplementary Information:**

The online version contains supplementary material available at 10.1186/s12962-024-00535-2.

## Introduction

Heart failure (HF) is a major global health challenge, affecting more than 64 million people worldwide [1]. It is a leading cause of mortality, morbidity, hospitalisation and healthcare costs, accounting for 1–3% of the total healthcare expenditure in European countries [2]. HF significantly impairs health-related quality of life (HRQoL) and is often associated with co-morbid other somatic and/or mental disorders [1, 3]. Integrated care has shown to be an effective way of dealing with the complexity of multimorbidity.

Various forms of integrated care, such as collaborative care (CC) or blended collaborative care (BCC), have shown to enhances primary care for individuals with anxiety disorders and depressive symptoms [4–6]. In addition, several sources suggest that integrated care approaches could lead to a reduction in care expenses thus offsetting (at least in part) the intervention costs [5, 7–12]. This reduction is assumed to result from the decline in formal caregiver visits (e.g. through improved coordination), which in turn is associated with fewer medical complications or hospitalisations [12, 13].

CC involves active follow-up by non-physician care managers who supports patients (e.g., by coordinating contacts, educating them about their illness, or proactively monitoring their responses to therapy). In contrast to CC which targets somatic or mental disorders, BCC interventions provide care for both conditions simultaneously [6, 14]. BCC has shown to improve both mental and physical health in patients affected by chronic somatic diseases with comorbid psychological distress such as anxiety disorders or depressive symptoms [6]. However, existing research in this area is limited and BCC interventions have not been specifically evaluated yet in European multimorbid patient populations [4].

The project ‘Evaluation of a patient-centred biopSychosocial blended collaborative CAre Pathway for the treatment of multimorbid Elderly patients (ESCAPE)’ (Horizon 2020 No. 945377) aims to develop and evaluate an integrated care pathway tailored to elderly patients experiencing somatic-mental multimorbidity, with a specific focus on HF patients [15]. The ESCAPE project includes a randomized-controlled trial (RCT) and a cohort study; both are taking place across eleven clinical centres in five European countries, including Denmark (Odense, Roskilde and Slagelse), Germany (Göttingen, Cologne, Leipzig, and Hamburg), Hungary (Budapest), Italy (Bologna), and Lithuania (Kaunas).

## Study objectives

The health economic part of ESCAPE was designed to investigate the economic impact of the BCC intervention and transfer these findings across the different jurisdictions represented by the participating countries. Furthermore, the results will support decision-making regarding the implementation of the BCC intervention. Specifically, the analysis aims to achieve the following:

To document the provision costs of the intervention,To assess the running costs of the intervention at the different trial sites,To evaluate the short-term cost-effectiveness and cost-utility of the ESCAPE BCC plus usual care intervention compared with usual care alone (based on the RCT data),To examine the budgetary implications of implementing the intervention in different health care systems practice.

## Methods and analysis

### Study design, study setting and selection of participants

Following the SPIRIT reporting guidelines, the study structure is described as a comprehensive cohort study including an embedded RCT. A more detailed description of the ESCAPE trial can be found in Zelenak et al. [15]. The RCT’s primary focus is to determine whether the addition of a 9-month optimised and targeted BCC intervention in elderly multimorbid patients to UC improves HRQoL compared to UC alone. For each treatment group, 150 patients aged 65 years or older with all types of confirmed HF, ≥ 2 chronic somatic comorbidities, and psychological distress or mental disorder were expected to be enrolled in the study. Among the five participating countries, the intended target enrolment target was assumed to range between 33 and 124 patients. In the intervention group, trained care managers supervised by multidisciplinary specialist teams provide pro-active support to patients and their informal carers to effectively manage their multiple health problems.

The trial is registered at the German Clinical Trials Register (DRKS00025120). The recruitment started at the coordinating site in Göttingen, Germany, in April 2022, with subsequent sites joining in the subsequent twelve months. The first patient was randomized in July 2022, and recruitment efforts are ongoing.

### Health economic analyses

Health economic evaluations are systematic assessments of the costs and effects of healthcare interventions or strategies. Their primary purpose is to inform decision-making by providing quantitative evidence on the comparative efficiency and value of different health care options [16, 17]. In the ESCAPE study, the trial-based economic analyses will include both a cost-effectiveness analysis (CEA) and a cost-utility analysis (CUA) with subgroup analyses for (i) depressive symptoms vs. no depressive symptoms and (ii) cardiovascular vs. no cardiovascular symptoms [16]. Evaluations will be made from a payer perspective.

### Cost-utility analysis

Where sufficient data are available, the calculation of QALYs for the CUA is done on a country-by-country basis using the EQ-5D-5L. The chosen index will be informed by national value sets specific to each country. As there is no value set for Lithuania, the closest available value set, i.e., Polish values, will be used due to its geographical proximity [18].

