### Medical costs and costs of providing the intervention

To facilitate a later implementation of BCC in practice, costs will be categorised into (i) those associated with the resource use and treatment of patients in the ECAPE intervention and (ii) those associated with the provision and maintenance of the intervention. Costs associated with patient resource use and treatment will be collected through iMCQ and/or health insurance data or flat rates for services. In Germany where claims data on patients’ medical costs will be available, these sources will be used to further corroborate the information obtained from the questionnaires, such as the iMCQ. This dual approach ensures data validation and should increase the accuracy and reliability of the economic evaluation. In Germany, patient receipts (based on Sect. 305 SGB V) include information on the services patients have received and the corresponding costs. German health insurance funds are obliged to provide these receipts to insured individuals, upon request. The participant signs an additional informed consent form that legally authorises the study staff to request data from health insurance companies. The subsequent data request and delivery process between the study team and the health insurance companies for all German sites will be centrally coordinated by the study centre in Göttingen in accordance with national regulations and data protection laws. Statutory health insurance (SHI) access is likely to be feasible mainly in Germany. Where cross-country comparisons are possible, results are converted into a common currency using purchasing power parity adjustments in order to account for differences in the cost of goods and services across countries [33].

The costs related to the provision of the intervention will reflect the resource use associated with the BCC intervention, i.e., costs related to the time spent by care managers, costs due to training and those of supervision. In addition, the costs of information and education materials for patients and their informal carers and the costs associated with the technological support (including the imergo® e-health ICP, network websites and interactive, multilingual patient websites) will also be considered.

Figure 2 provides a detailed overview of the intended structure of the economic evaluation, including the outcome measures, and the identification of resource use and costs.

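### For cross-country or pooled cost per QALY, national EQ-5D-5L value sets alone do not separate health effect from value set; add a common-set valuation

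*Protocol article*

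**What the plan says.** The protocol article, section Cost-utility analysis, sets the level and scale of valuation: "Where sufficient data are available, the calculation of QALYs for the CUA is done on a country-by-country basis using the EQ-5D-5L", and "The chosen index will be informed by national value sets specific to each country". One country is an exception: "As there is no value set for Lithuania, the closest available value set, i.e., Polish values, will be used due to its geographical proximity".

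The cross-country intention appears in two places. Under Methods, the Abstract says: "The trial-based economic analyses will include cross-country cost-effectiveness and cost-utility assessments from a payer perspective". Under Study objectives, one aim is to "transfer these findings across the different jurisdictions represented by the participating countries".

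Costs have a stated route to a common scale, which is conditional (Medical costs and costs of providing the intervention): "Where cross-country comparisons are possible, results are converted into a common currency using purchasing power parity adjustments".

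The section Uncertainty and validity names non-parametric bootstrapping, cost-effectiveness planes and acceptability curves. The article names no valuation of all patients with one common set, either as base case or as sensitivity analysis.

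**The concern.** A value set turns five EQ-5D-5L answers into one utility. If two countries use different sets, two patients with the same answers and the same change over time receive different QALY gains. For a national payer that is intended, because national preferences are part of what is being valued. Between countries, a difference in cost per QALY then has at least two possible sources: the intervention changed health by different amounts, or the same change was valued differently. As written, the plan offers nothing that tells them apart.

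The same applies to any pooled estimate. Country-level QALYs are planned only where data suffice, and country enrolment targets run from 33 to 124. If data were pooled for that reason, the QALY difference would average over several scales, with weights set by recruitment.

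At stake is the reading of the cross-country cost-utility result and of how well it transfers. The trial's randomised comparison is not at stake.

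**Working it through.** **Figure to reproduce.** There is none. The article gives no value-set coefficients, utility effect, standard deviation or incremental cost. The arithmetic below shows the mechanism under labelled assumptions.

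**Inputs from the article**
- Treatment period: 9 months = 0.75 year (Outcome measures).
- 150 patients per group, 300 in total; country targets between 33 and 124 (Study design, study setting and selection of participants). These fit together: 300 − 33 − 124 = 143 for the other three countries, a mean of 47.7.

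**Assumptions**
- d = 0.05: between-arm utility difference at 9 months on a reference scale, the same health effect in every country.
- k: scale of a national value set relative to the reference. A single multiplier is a simplification, since sets can also weight the dimensions differently.
- Incremental cost of 500 PPP units in every country.
- Equal baselines and linear change over the 9 months.

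**Step 1: effect of the value set on cost per QALY**

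Incremental QALY = 0.5 × 0.75 × k × d = 0.01875 × k. Cost per QALY = 500 / (0.01875 × k).

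| Spread of k | Incremental QALY | Cost per QALY | Ratio |
|---|---|---|---|
| none (k = 1, common set) | 0.01875 | 26,667 | 1 |
| 0.9 to 1.1 | 0.0169 to 0.0206 | 29,630 to 24,242 | 1.1/0.9 = 1.22 |
| 0.8 to 1.2 | 0.0150 to 0.0225 | 33,333 to 22,222 | 1.2/0.8 = 1.5 |
| 0.7 to 1.3 | 0.0131 to 0.0244 | 38,095 to 20,513 | 1.3/0.7 = 1.86 |

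The ratio depends only on k. It is the same for d = 0.03 or 0.10 and for any common incremental cost.

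**Step 2: do the planned methods reveal this?**
- PPP conversion acts on the numerator. It leaves k in the denominator.
- Resampling patients leaves each country's value set fixed, so k is the same in every replicate and the acceptability curve inherits it.
- One common set for all patients gives k = 1 throughout, and in this illustration the spread vanishes.

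**Step 3: comparison with sampling error**

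The standard error of a between-arm utility difference in a country of n patients, 1:1, is SD × √(4/n). The SD is assumed to be 0.2 to 0.3.
- n = 33: 0.0696 to 0.1044.
- n = 124: 0.0359 to 0.0539.
- Difference in effect between two such countries: √(0.0696² + 0.0359²) = 0.078, to √(0.1044² + 0.0539²) = 0.118.

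The value-set contribution on the same utility scale is d × (difference in k): 0.05 × 0.2 = 0.01, 0.05 × 0.4 = 0.02 and 0.05 × 0.6 = 0.03 for the three spreads. Under these assumptions it is smaller than the sampling error between those two countries.

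**The case against.** The strongest reply is that the plan does what a payer-perspective evaluation should do. It values health with each country's own preferences, calculates QALYs country by country, and converts currency only where comparison is possible. Prices and preferences are different things, so adjusting one does not oblige the plan to adjust the other. The cross-country aim also covers hospital admissions avoided and depression-free days, which need no value set. Sampling error would probably swamp the artefact. A fuller health economic plan may already contain a common-set analysis.

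Much of this stands. National sets are a sound choice for national decisions, and the other two endpoints are unaffected. Step 3 supports the point on sampling error, but the two errors differ in kind: the bootstrap displays sampling error and more patients reduce it, while the value-set difference is systematic and hidden. A fuller plan may indeed fill the gap. Even so, this article is the health economic protocol, and it fixes both the valuation rule and the cross-country cost-utility aim.

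Three stronger readings are tempting and are not supported:
- A reader might infer that the design cannot separate health effect from value set. It can: the EQ-5D-5L is collected from all patients at all three time points and can be re-scored.
- A reader might infer that the treatment comparison is biased. Within a country both arms share one set, so it is not.
- A reader might infer that a pooled ICER or a ranking of countries is planned. The article states neither; pooling is only a possible response to insufficient country data.

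**Conclusion.** The point holds within limits. For a cross-country cost-utility comparison, and for any pooled cost per QALY, the plan as written leaves differences in health effect mixed with differences in value set, and neither PPP conversion nor the bootstrap addresses this. Country-specific analyses are sound as planned.

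The size is unknown from the documents. The 1.22- to 1.86-fold range rests wholly on assumed scale differences of ±10% to ±30%, a single scale multiplier, and equal health effect and cost across countries. With an assumed SD of 0.2 to 0.3, sampling error between a country of 33 and one of 124 would exceed the artefact. The documents therefore do not show that any country would look better or worse solely because of its value set. This is an inexpensive improvement to a stated aim, not a flaw in the trial.

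**What to change.** Keep the national value sets for every country-specific cost-utility analysis. For any cross-country comparison or pooled cost per QALY, also value all patients' EQ-5D-5L responses with one common value set, named before the data are analysed, and report that result beside the national-set result. For Lithuania, where geographical proximity is the stated ground for the proxy, add at least one alternative set as a sensitivity analysis. Repeating everything under each national set is optional.

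The cost is re-scoring of responses already being collected and one extra table. The downside is that the common-set figure will not match the national analyses, so the report must say which figure answers which question. Recruitment was still open when the article was written, and its Discussion allows partial changes to the analysis plan, so the addition could be prespecified.

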### Cost-effectiveness analysis

As the expected benefit of the BCC intervention may not be reflected in a corresponding gain in QALYs, two additional CEAs will be performed: (i) for all patients, the cost per hospital admission avoided; (ii) for individuals with a given level of depressive symptoms, the cost per depression-free day (DFD), with DFDs as the number of days per annum a patient is depression-free. The different incremental cost-effectiveness ratios (ICERs) will be calculated as follows:

The cost per hospital admission avoided is calculated by comparing the healthcare utilisation of the BCC intervention with that of UC alone and across different subgroups with cardiovascular symptoms identified from the Kansas City Cardiomyopathy Questionnaire (KCCQ-12). The calculation of the DFDs will be based on data acquired from the HADS. Calculating DFDs, the translation of the HADS scores into DFDs will be based on the conversion method outlined by Lave et al. [19]. Details of the conversion method are outlined in the section ‘Subgroup analyses’.

Figure 1 provides an overview of the intended structure of the economic evaluation, and each aspect is explained in detail below.

**Fig. 1 Fig1:**
[figure not shown]
Planned economic evaluation in the ESCAPE study

### Data collection

#### Outcome measures

Clinical effects will be measured using the EQ-5D-5L, HADS, and KCCQ-12 instruments at three specific time points: during the baseline assessment and randomisation phase (BL), at the ‘end of treatment’ in the RCT after 9 months (FU1), and finally, at the ‘end of study’ evaluation, which will take place 18–33 months after enrolment (FU2).

The **EQ-5D-5L** index will be used as a tool to gauge QALYs [20, 21]. The EQ-5D-5L, designated as the primary outcome of the main study, includes dimensions such as mobility, self-care, usual activities, pain/discomfort, and anxiety/depression. It has been used in a wide range of studies across Europe and in different populations including multimorbid and older people [22, 23]. This index has been linguistically validated and exhibits satisfactory sensitivity to change.

The **KCCQ-12** is a concise 12-item patient-reported instrument designed to assess the quality of life and functional status of individuals with HF. It quantifies various domains, such as physical limitations, symptoms, self-care, and social limitations, providing a comprehensive picture of a patient’s cardiac health-related well-being [24].

The **HADS** will be used to assess a patients’ psychological distress. This scale, which has also been used in medical studies with patients with heart disease, produces separate scores for severity of anxiety and depression symptoms [25]. Overall psychological distress is measured by the total score, ranging from 0 to 42, with a score exceeding 12 assumed to detect at least mild levels of prognostically relevant distress.

### Resource use and costs

Data on resource use and costs associated with the BCC intervention will be obtained from multiple sources and standardised approaches, as the feasibility of accessing medical records and the costs vary from country to country. The imergo® e-health Integrated Care Platform (ICP) will be used to collect study-related medical information and to further enhance the data collection process for patients assigned to the intervention group throughout the study. Patient-related and provider-related utilisation will be measured by applying a time-driven activity-based costing (TDABC) approach [26]. The TDABC will streamline the care process by focusing on the time required to execute activities along the care pathway. Corresponding costs will be assigned to specific activities by multiplying the time invested in an activity by the corresponding capacity cost rate of the resources involved [27–30]. Table 1 provides an overview of possible methods for collecting costs and resources.

**Table 1 Tab1:** Potential methods for collecting costs and resources

Sites	Patient-related		Provider- and study-related	
	Health insurance data (utilisation and costs)	Medical consumption (only utilisation)	imergo® e-health ICP (study-related medical records and assessments)	Care manager survey (provider-related resources)
Germany	Patient receipts	-	x	x
Denmark	Possible	iMCQ	x	x
Italy	tbd	iMCQ	x	x
Lithuania	tbd	iMCQ	x	x
Hungary	tbd	iMCQ	x	x

### Patient-related utilisation: medical consumption questionnaire (iMCQ)

Patient-related resource utilisation will be assessed using the iMCQ, medical records and study data retrieved from the external clinical information system secuTrial and the imergo® e-health ICP. The iMCQ will cover all healthcare services provided to individual patients which are not part of the intervention. In order to reduce the participants’ burden of study-specific processes, questions of limited relevance were excluded in accordance with the prescribed questionnaire guidelines [31]. Similarly, the medication chart has been adapted as the task of documenting medication details will be entrusted to the care managers. The iMCQ will be administered at the start of the RCT, at the 9-month point (i.e., end of treatment), and at the ≥ 18-month milestone (i.e., end of study). The retrospective iMCQ will record the patient’s medical consumption over the last 3 months. As it is not feasible to administer the iMCQ quarterly, patient-related utilisation will be determined based on available evidence and agreed upon by clinical experts. Resource utilisation will be extrapolated to the 9-month intervention or 18 to 33-month follow-up period. The iMCQ will not be implemented in Germany, as patient receipts cover costs and medical consumption.

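### Outside Germany, medication is to be recorded by care managers, who are described only for the intervention arm, and no matching usual-care source is named, so incremental cost is at risk of differential measurement

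*Protocol article*

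**What the plan says.** All places are in the protocol article.

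- **Medication.** The iMCQ section says that "the medication chart has been adapted as the task of documenting medication details will be entrusted to the care managers". It does not say what the adapted chart still asks.
- **Care managers.** The study design section places them in one arm: "In the intervention group, trained care managers supervised by multidisciplinary specialist teams provide pro-active support to patients and their informal carers". The care manager survey section describes their work as activities that make up the intervention.
- **Sources of patient-related utilisation.** The iMCQ section states: "Patient-related resource utilisation will be assessed using the iMCQ, medical records and study data retrieved from the external clinical information system secuTrial and the imergo®". The platform named last is the ICP. The section on resource use and costs says the ICP serves "to further enhance the data collection process for patients assigned to the intervention group throughout the study".
- **Scope of the iMCQ.** "The iMCQ will cover all healthcare services provided to individual patients which are not part of the intervention".
- **Germany.** "The iMCQ will not be implemented in Germany, as patient receipts cover costs and medical consumption". No restriction by arm is stated for the receipts.
- **Other countries.** Table 1 gives the iMCQ for Denmark, Italy, Lithuania and Hungary. Health insurance data are only possible in Denmark and undecided in the other three.
- **Comparison.** The third objective includes the "cost-utility of the ESCAPE BCC plus usual care intervention compared with usual care alone (based on the RCT data").

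**The concern.** Incremental cost is a difference between arms, so each component has to be measured in the same way in both. Here one component, medication, is moved from a questionnaire with no stated arm restriction to staff whose described contact is with intervention patients. The ICP raises the same question for other utilisation, because it is named as a source although its added data collection is for the intervention arm.

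A difference in recording is systematic error. The planned bootstrap resamples the recorded data, so it reproduces the error and does not widen the interval to reflect it. All the planned cost-effectiveness ratios share the incremental cost as numerator. If admissions were also counted from the ICP, the effect measure for cost per admission avoided would be affected too. An analysis plan cannot restore usual-care medication data that were never collected.

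**Working it through.** The article gives no drug cost, capture rate or economic sample size, so there is no stated figure to reproduce. The check sets the passages side by side and then gives the form that an error would take.

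**Who records medication, by arm and country**

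| | Intervention | Usual care |
|---|---|---|
| Germany | patient receipts | patient receipts |
| Denmark, Italy, Lithuania, Hungary | care managers, plus the adapted iMCQ chart | the adapted iMCQ chart; nobody named for the part moved to care managers |

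secuTrial and medical records are listed without an arm restriction, but the article does not say whether they hold medication data.

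**Inputs from the document.** 150 patients per arm, 300 in total. Country targets range from 33 to 124; the German target is not given.

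**Assumptions.** The true mean drug cost D is the same in both arms and in all countries, and the arms are balanced within country. Capture is complete in the intervention arm (c1 = 1), and usual-care capture c0 is varied.

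**Formulas**

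- Spurious incremental drug cost at non-German sites = (c1 − c0) × D.
- Pooled over all countries = non-German share × (c1 − c0) × D.
- Non-German share if Germany enrols 124: (300 − 124)/300 = 176/300 = 0.587.
- Non-German share if Germany enrols 33: (300 − 33)/300 = 267/300 = 0.890.

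**Results, as a percentage of D**

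| Usual-care capture c0 | Non-German sites | Pooled |
|---|---|---|
| 1.00 | 0 | 0 |
| 0.90 | 10 | 5.9 to 8.9 |
| 0.75 | 25 | 14.7 to 22.2 |
| 0.50 | 50 | 29.3 to 44.5 |
| 0 | 100 | 58.7 to 89.0 |

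With the same capture in both arms the spurious increment is zero, whatever the level of capture.

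**The case against.** The strongest reply is that the article leaves a detail unstated and does not describe a bias. The chart was adapted, and nothing says that medication was taken out of the iMCQ; the same section gives the iMCQ a scope covering all services outside the intervention. secuTrial and medical records carry no arm restriction and may hold usual-care medication. The content of case report forms would normally be found in the main trial protocol, which is not shown. No sentence forbids care managers from recording medication in usual care.

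The ICP part is weaker still. Table 1 files the ICP under provider- and study-related data. The section on medical costs names the iMCQ, insurance data or flat rates for patient costs and does not mention the ICP. Its use for counting care-management contacts is proper, because those are intervention costs.

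Much of this stands. A reader might infer that drug costs are charged to one arm only, or that intervention patients will appear to have more admissions. The documents support neither: the first needs removal of the chart and no other source, and no text says that admissions will be counted from the ICP.

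A reader might also put a large figure on the ratio. Assume drug costs of 600 to 1,500 currency units per year, hence 450 to 1,125 over 9 months (× 0.75), and a QALY gain of 0.05 × 0.75/2 = 0.01875. With no usual-care capture and no German patients, the shift would be 450/0.01875 = 24,000 to 1,125/0.01875 = 60,000 per QALY. Multiplying by the non-German share gives about 14,000 to 53,000, and with 90% usual-care capture about 1,400 to 5,300. None of the cost, utility or capture inputs is in the document, so these figures are not findings.

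What the reply does not remove is that the article gives a reason for altering the chart, and that reason covers only the arm that has care managers. It describes how data are collected, which is more than an omission, and outside Germany Table 1 commits to no other source of patient-related data.

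**Conclusion.** The point holds as a risk. Followed as written, the plan allows medication, and possibly other utilisation, to be captured differently by arm in four of the five countries, and nothing in the article shows that another source closes the gap. That care managers do not record usual-care medication is a strong inference, not a stated fact.

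Neither size nor direction can be derived from the document. The error is zero if secuTrial or medical records capture both arms equally. Otherwise it is the difference in capture times the drug cost at non-German sites, and 59% to 89% of that when pooled, on the assumptions of equal true drug cost and balance within country. If usual-care drugs are the ones under-recorded, the intervention looks dearer than it is. The German receipts are not affected through this route.

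**What to change.** 1. Record medication from one source in both arms, with the same recall window and at the same times (baseline, 9 months, end of study), by staff other than care managers. If an existing secuTrial form already covers both arms, use it and say so; one sentence then settles the medication point. Otherwise use the iMCQ medication chart at the remaining visits.
2. Base all between-arm utilisation, including admissions, only on sources applied identically to both arms. Use ICP and care-manager records only to cost delivery of the intervention, and reconcile the iMCQ section with Table 1 and the section on medical costs accordingly.
3. Where usual-care medication was not recorded comparably, report costs without medication in both arms, and show results including medication as a sensitivity analysis.

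**Cost.** A few minutes at visits already scheduled and a short addition to the plan. The first patient was randomised in July 2022, so visits already completed cannot be recovered. At sites where medication is left out, the base case omits a payer cost that the intervention might itself change, and this should be stated as a limitation.
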